## Abstract

**Background:**

One of the most difficult symptoms for persons with sickle cell disease (SCD) to manage is chronic pain. Chronic pain impacts approximately one-third of persons with SCD and is associated with increased pain intensity, pain behavior, and frequency and duration of hospital visits. A promising category of nonpharmacological interventions for managing both physical and affective components of pain are mindfulness-based interventions (MBIs).

**Methods/design:**

The primary aim of this study is to conduct a randomized controlled study to evaluate the acceptability and feasibility, as well as to determine the preliminary efficacy, of a telephonic MBI for adults with SCD who have chronic pain. We will enroll 60 adult patients with SCD and chronic pain at an outpatient comprehensive SCD center in the southeastern United States. Patients will be randomized to either an MBI or a wait-listed control group. The MBI group will complete a six-session (60 minutes), telephonically delivered, group-based MBI program. The feasibility, acceptability, and efficacy of the MBI regarding pain catastrophizing will be assessed by administering questionnaires at baseline and weeks 1, 3, and 6. In addition, ten randomly selected MBI participants will complete semistructured interviews to help determine intervention acceptability.

**Discussion:**

In this study protocol, we report detailed methods of the randomized controlled trial. Findings of this study will be useful to determine the acceptability, feasibility, and efficacy of an MBI for persons with SCD and chronic pain.

**Trial registration:**

ClinicalTrials.gov identifier: NCT02394587. Registered on 9 February 2015.

**Electronic supplementary material:**

The online version of this article (doi:10.1186/s13063-017-1948-x) contains supplementary material, which is available to authorized users.

## Background

Sickle cell disease (SCD) is a genetic hematological disorder that affects more than 7 million people globally [1, 2]. It is estimated that 50% of adults with SCD experience pain on most days, with one-third experiencing chronic pain daily [3]. In addition to debilitating chronic pain [2, 4], persons with SCD experience acute pain episodes known as *vaso-occlusive crises* (VOCs). A VOC is caused by an accumulation of sickled red blood cells in the vasculature, resulting in damage (acute pain) to surrounding tissue areas [5]. In addition to pain caused by VOCs, it is common for persons with SCD to catastrophize pain (feelings of helplessness, pain rumination and magnification) and experience anxiety and depression [6, 7]. A promising category of nonpharmacological interventions for managing both physical and affective components of pain are mindfulness-based interventions (MBIs [8, 9]).

There is strong evidence to support the use of MBIs for persons with chronic pain [10, 11]. MBIs teach patients that sensing pain, even if it is intense or chronic, does not need to be fought, ignored, or suppressed or need to inhibit them from living a meaningful life or accomplishing their goals [12]. This approach challenges patients to decrease pain-related cognitive and emotional reactivity that can increase distress and exacerbate pain (e.g., pain catastrophizing) and to engage in active coping in the present moment [13]. The mindfulness approach is thus very different from other types of nonpharmacological therapies such as cognitive behavioral therapy (CBT). In CBT, a patient is taught to recognize and reframe negative thought patterns to change how they are feeling (e.g., analyzing thoughts; [14]), whereas in an MBI, the patient is taught not to reframe negative thoughts but to notice and accept thoughts (e.g., experiencing thoughts) and then redirect their focus to the present moment [15]. MBIs can thus be viewed as more of a naturalistic observation or participant observation (open monitoring) of thoughts vs. a purposeful reframing of thoughts as in CBT. For both approaches, multiple systematic and Cochrane reviews on their utility for pain and pain coping have been published, which largely support the use of both MBI and CBT approaches [16, 17].

Whereas MBIs have shown positive effects, the generalizability of these results for persons with SCD is unknown [18]. Some MBIs (e.g., mindfulness-based stress reduction [MBSR]) require eight weekly classes, homework assignments, and daily practice (30–45 minutes per day), which may be too much of a burden for persons with SCD and chronic pain. Second, missed clinic appointment rates for persons with SCD are reportedly as high as 46% [19], so it is unknown if persons with SCD are able to adhere to a weekly MBI schedule. Third, persons with SCD are not typically prescribed nonpharmacological interventions. Many persons with SCD are prescribed hydroxyurea and chronic opioids to manage their disease and have little exposure to additional therapeutic interventions, with the most common alternative therapy used by persons with SCD being prayer [20]. Last, the majority of current MBIs have been developed and tested with nonminority (Caucasian) sample populations, so there is uncertainty whether an MBI would be seen as acceptable, feasible, or effective in a predominately minority sample (e.g., African Americans with SCD). To our knowledge, no study to date has investigated the feasibility or acceptability of an abbreviated MBI delivered telephonically for persons with SCD and chronic pain [21]. In this paper, we report detailed methods of our clinical trial design.

### Research objectives

The overall goals of this pilot randomized controlled clinical trial (RCT) are to explore the feasibility and acceptability of an abbreviated six-session MBI that is targeted for persons with SCD and chronic pain and to obtain preliminary data on the efficacy of this intervention relative to a wait-listed control condition on pain catastrophizing and other pain-related outcomes. The specific aims are to (1) evaluate the feasibility and acceptability of the telephonic MBI designed to reduce pain-catastrophizing symptoms for adults with SCD and chronic pain and (2) determine preliminary efficacy of the MBI relative to the control condition on pain catastrophizing as well as pain interference and severity, depression, health-related quality of life (mental and physical health), and mindfulness

## Methods/design

### Overview

We are conducting a single-site pilot RCT comparing MBI and a wait-listed control condition with assessments at four time points (baseline, week 1, week 3, and week 6) in adult patients with SCD and chronic pain. Individuals who provide written informed consent will be enrolled and randomized to an MBI or control condition. The MBI will be conducted as a ten-person group teleconference call led by a certified MBI instructor. A 2:1 treatment allocation will be implemented in this initial pilot study to collect more data on the feasibility and acceptability of the MBI. Feasibility will include measures of enrollment, randomization, attendance, and intervention completion along with assessment completion. Acceptability will be assessed with semistructured interviews conducted with randomly selected MBI participants. The primary efficacy outcome will be pain catastrophizing total score.

#### Setting and sample

Patients will be recruited from an outpatient comprehensive SCD center in the southeastern United States. An interdisciplinary team of physicians, nurses, psychologists, and social workers run the center, providing care for approximately 600 adults with SCD. The target sample for this pilot study is 60 patients with SCD and chronic pain, with 40 patients randomly assigned to receive the MBI and 20 patients to the control condition. With a sample size of 60, the study does not have 80% power to detect a significant difference between the MBI and control conditions on the primary outcome of pain catastrophizing with a level of significance set a 0.05 (two-tailed). However, the focus of this pilot study is to estimate treatment effect sizes rather than to conduct statistical significance testing.

### Eligibility criteria

Patients meeting the following criteria will be eligible for inclusion: (1) self-reported diagnosis of SCD; (2) be age 18 years or older; (3) self-identified as having chronic, noncancer pain that has persisted on most days for more than 6 months and adversely affects function or well-being; (4) possess the ability to speak and read English; (5) have access to a landline or cell phone; and (6) have access to a compact disc (CD) or MP3 player. Patients will be excluded if they (1) previously participated in an MBI study (e.g., MBSR, mindfulness-based cognitive therapy or intervention) or (2) regular practitioners of mindfulness, including yoga.

### Recruitment

Recruitment letters will be mailed in waves of 50 to patients with a scheduled appointment at the outpatient center within 2 weeks of their appointment. This decision was made because there is no rigorous method to determine which patients are experiencing chronic pain. The recruitment letter will explain the study purpose, inclusion criteria (including definition of chronic pain), and participant involvement and provide contact information for the study principal investigator (PI). On the basis of previous research experience in the center, including poor response to recruitment letters, the recruitment letter will use institutional review board-approved opt-out language to notify patients that the PI will contact them via phone to describe the study, unless the patient informs the PI via phone or email that he or she does not want to be contacted. A period of 2 weeks will be provided prior to initiating phone calls after the mailing is sent to allow potential subjects time to contact the PI. Three attempts to contact the patient will be made before determining that the patient is not interested in participating. The same recruitment script used for in-person recruitment will be used to discuss the study with potential subjects by phone. Individuals who meet all inclusion criteria and verbally agree to participate will be mailed a consent form along with the study packet.

In-person recruitment will occur immediately before or after a patient’s clinic appointment. Prior to being approached by study personnel, patients will be prescreened by their healthcare provider and a study staff member to assess their general capacity to participate (e.g., ability to provide consent), current involvement in other research studies, and if they have already been mailed a recruitment letter. Patients already enrolled in a cognitive or behavioral intervention study will not be approached for recruitment, owing to the potential of carryover effects between interventions. A recruitment script will be used to discuss the study with potential participants, verify the presence of chronic pain per the study definition, and solicit participation. Individuals who meet all inclusion criteria and verbally agree to participate will then sign a consent form and receive a study packet containing a copy of the consent form, a set of headphones, a mindfulness practice CD, and four copies of assessments. For participants who have an email address, identical digital versions of the questionnaires will be provided through hyperlinks managed with REDCap electronic data capture tools [11].

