### Randomization procedures

Patients who provide informed written consent and meet the participant selection criteria will be enrolled and randomized using a 2:1 treatment allocation to either the MBI or control condition. Because the MBI condition is group-based, randomization of participants will be divided into 4 cohorts of 15 participants to reduce the amount of idle time between informed consent and intervention delivery. After the first cohort of 15 participants provides informed consent, they will be randomly assigned either to receive the MBI (*n* = 10) or to a control condition (*n* = 5). The random number function in Excel 2007 software (Microsoft, Redmond, WA, USA) will be used to randomize patients to either the MBI (*n* = 40) or control (*n* = 20) condition using a permuted block randomization scheme to achieve a 2:1 allocation. Within each block size of 15, 10 patients will be randomized to receive the MBI and 5 will be randomly assigned to the wait-listed control condition.

Within 2 weeks of randomization, participants will begin the MBI or their time in the control condition. Following randomization and initiation of the first cohort of 15 patients, the next cohort of 15 patients will be recruited and randomized following the same protocol. This will continue until 60 participants are randomized in a total of 4 cohorts.

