#### Wait-listed control condition

Patients randomized to the control condition will not receive the MBI but will receive treatment as usual. Treatment as usual consists of standard medication management as prescribed by the subject’s hematologist, primary care physician, psychologist, and/or any other medical professionals overseeing treatment.

Wait-listed patients will be offered the opportunity to cross over to the MBI condition once patients in the intervention arm complete six sessions. Patients who cross over from the wait-list to the MBI will participate in the same protocol as patients originally randomized to the MBI condition. The schedule of enrollment, interventions, and assessments of this study is shown in Fig. 1 and the Standard Protocol Items: Recommendations for Interventional Trials (SPIRIT) checklist (*see* Additional file 1).

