### Acceptability

Acceptability will be assessed qualitatively. Semistructured interviews will be performed with ten randomly selected participants from the MBI condition within 2 weeks of the final MBI session by telephone to assess acceptability and help interpret quantitative findings related to the exploratory aim [38]. Each MBI participant who completes at least one MBI session will be randomly assigned a number using the random number function in Excel 2007 and then ordered in an ascending fashion. The participant with the lowest number will be contacted first, followed by the participant with the next lowest number, and so forth. Two to three participants will be selected from among each of the four cohorts. Each interview will be conducted by one study staff member who is familiar with the content of the MBI. The interview will consist of the questions listed in Table 2.

**Table 2 Tab2:** Semistructured postinterview questions

Q1	Tell me about how easy or difficult it was for you to complete the weekly telephone-based MBI sessions?
Q2	What impact, if any, do you feel the MBI program had on (a) your perceptions on chronic pain, and (b) your quality of life?
Q3	What did you find most useful about the MBI program?
Q4	What did you find least useful about the MBI program?
Q5	What would you want more of in the MBI program?
Q6	What would you eliminate or have less of in MBI program?
Q7	Tell me about how easy or difficult it was for you to practice mindfulness, and complete the homework assignments?
Q8	Do you intend to continue using this MBI?
Q9	Would you recommend a MBI to friends with SCD who also experience chronic pain?
Q10	Is there anything else that you would like me to know about your experience?

*MBI* Mindfulness-based intervention, *SCD* Sickle cell disease

This table provides a list of questions that will be asked of study participants who are randomized to the experimental condition, and it will be administered at the end of the 6-week MBI

Because we were unable to find any literature on the subjective experiences of persons with SCD and chronic pain who participated in a mindfulness intervention, the guiding questions listed in Table 2 will be used to roughly structure conversations, allowing digression into other topics brought up by the participants. Interviews will be digitally recorded, and we anticipate that they will last between 30 and 60 minutes.

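### The mindfulness practice CD goes out at consent, before randomization, so wait-listed controls hold practice material during the comparison; any use that helps them biases the effect toward zero by an unknown amount

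*Protocol article*

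**What the plan says.** Four places in the protocol article bear on this.

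- **Recruitment, in person.** After signing consent, patients "receive a study packet containing a copy of the consent form, a set of headphones, a mindfulness practice CD, and four copies of assessments".
- **Recruitment, by mail and telephone.** Patients who meet the criteria and "verbally agree to participate will be mailed a consent form along with the study packet". The contents are not listed again here. I read it as the same packet.
- **Randomization procedures.** Allocation comes later: "After the first cohort of 15 participants provides informed consent, they will be randomly assigned", ten to the MBI and five to control, in four such cohorts.
- **Wait-listed control condition.** "Patients randomized to the control condition will not receive the MBI but will receive treatment as usual". Usual care is then described as medication management by the patient's own clinicians. Controls may cross over once the intervention arm has finished its six sessions.

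Two further details show that the CD is usable and relevant. Eligibility criteria require every participant to "have access to a compact disc (CD) or MP3 player". The interview guide under Acceptability asks MBI participants "Tell me about how easy or difficult it was for you to practice mindfulness, and complete the homework assignments", so home practice is treated as part of the programme.

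**The concern.** Material issued before allocation reaches both arms. Controls are meant to be free of the intervention, yet they would have a practice aid and headphones in hand from consent until the end of the six-week comparison. Nothing in the article holds the CD back from them or asks them to leave it unused, and the assessment schedule (Table 3) has no item on its use.

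The protocol itself treats such exposure as a threat. Patients already in another cognitive or behavioural intervention study are not approached because of possible carryover, and earlier MBI participants and regular mindfulness practitioners are excluded.

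What is at stake is the estimate of the MBI effect on the PCS total score. Setting and sample and Analytic approaches both say that the pilot is meant to estimate the effect rather than to test it. Control practice that helps would make that estimate too small. The confidence interval would not show this, and without a record of use it could not be examined afterwards.

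**Working it through.** **Step 1: the plan's own figures.** The cohort arithmetic holds: 4 × 10 = 40 MBI and 4 × 5 = 20 control, total 60. The statement that 60 patients do not give 80% power at two-sided 0.05 cannot be reproduced as a number, because no difference or SD is given. In standardized units the standard error of the difference is √(1/20 + 1/40) = 0.274, and the difference detectable with 80% power is (1.960 + 0.842) × 0.274 = 0.77 SD. The statement is therefore true for any standardized difference below about 0.77.

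**Step 2: order of events.**

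| Event | Section | Arm known? |
|---|---|---|
| Packet with CD and headphones handed over (in person) | Recruitment | No |
| Packet mailed with the consent form (telephone route) | Recruitment | No |
| Cohort of 15 complete, then randomized | Randomization procedures | From here |
| MBI or control period starts within 2 weeks of randomization | Randomization procedures | Yes |
| Assessments at weeks 1, 3 and 6 | Efficacy, Table 3 | Yes |

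The packet precedes allocation on both routes, so the plan as written gives the CD to future controls as well as to future MBI patients.

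**Step 3: direction and possible size of the dilution.** Let u be the share of controls who use the CD and s the share of the full MBI effect that such use brings. Then

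observed effect = true effect × (1 − u × s).

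If a later trial is sized on the observed effect, its sample size is multiplied by 1/(1 − u × s)². The documents give neither u nor s, so every row is an assumption.

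| u | s | Attenuation u × s | Observed effect if the true effect is 0.50 SD | Sample-size multiplier |
|---|---|---|---|---|
| 0 | any | 0% | 0.50 | 1.00 |
| 10% | 25% | 2.5% | 0.49 | 1.05 |
| 25% | 25% | 6.25% | 0.47 | 1.14 |
| 25% | 50% | 12.5% | 0.44 | 1.31 |
| 50% | 50% | 25% | 0.375 | 1.78 |
| 75% | 50% | 37.5% | 0.31 | 2.56 |

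The true effect of 0.50 SD is also an assumption, used only to give a scale.

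**Step 4: comparison with random error.** The 95% confidence half-width at 40:20 is 1.96 × 0.274 = 0.54 SD. The largest assumed dilution at a true effect of 0.50 SD is 0.50 × 0.375 = 0.19 SD, well inside that half-width.

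**Step 5: baseline.** The CD and the assessment forms arrive in the same packet, and Feasibility allows two weeks from recruitment to complete baseline. Practice could therefore come before baseline, whereas the Efficacy section places baseline ahead of any treatment. Before allocation nobody knows their arm, so such practice shifts both arms equally in expectation.

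**The case against.** The strongest reply has four parts.

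*The CD is not the MBI.* The intervention is defined as six instructor-led telephone group sessions. Neither its description nor Table 1 lists the CD, and the CD's contents are not described. A control who holds it has not received the MBI so defined. This stands in part: controls hold at most a portion of the intervention, and the conflict with the control section is not word for word. But a mindfulness practice CD is not medication management, and the interview guide treats practice and homework as belonging to the programme.

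*Holding is not using.* A reader might infer that all 20 controls were exposed in effect, or that the trial really compares sessions plus CD with CD plus usual care. The documents support neither inference. They show access, not use. Even universal access rests on reading the mailed packet as the one listed for in-person recruits.

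*The bias is small, conservative and secondary.* It runs toward no difference, lies within the random error, and leaves the feasibility and acceptability aims untouched. All of this is true. Random error, however, is symmetric and shows in the interval. This error has one direction and does not show.

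*A condensed article omits handling instructions.* The full protocol or manual may say when the CD is to be opened. That is possible, and the absence of such instructions is not the point here. The point is the distribution step that the article states, which puts the CD in control hands before allocation.

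**Conclusion.** The point holds as a design weakness of unknown size. Followed as written, the plan gives wait-listed controls mindfulness practice material for the whole comparison period, and any beneficial use biases the MBI-versus-control effect on PCS toward zero. The attenuation could be nil; under the assumptions shown it reaches about 38%. No single figure or narrower range can be taken from the documents, and a range that leaves out low or zero use would overstate what is known.

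A reader might also infer that early practice lowers the MBI arm's baseline and so hides part of its change. That does not follow. Practice before allocation affects both arms alike, so baseline may not be strictly pre-treatment, but the bias is not specific to the MBI arm.

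The conclusion rests on two readings: that the mailed packet matches the in-person one, and that the CD carries usable practice content, as its name says.

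**What to change.** - Take the CD and headphones out of the consent packet. Send them to the MBI arm only, after allocation and once the baseline form has been received. Send them to controls only after their week-6 assessment, which also serves those who cross over. The cost is one extra mailing to 40 MBI patients, a later one to up to 20 controls, and a short amendment to Recruitment.
- Trial status says that recruitment has ended. For packets already sent, add a question on CD use in both arms if participants can still be reached. State in the report that controls had access to the practice CD, so the contrast may be diluted. Do not state that controls used it unless the data show it.
- If in practice the CD was sent only after allocation, correct the packet description under Recruitment. That costs one sentence and settles the matter.
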